### Power

While the primary outcome variable of the study is a participant’s score on the PHQ-9 (a continuous measure), power calculations were based on rates of caseness for MDD as a larger sample is required to be able to detect changes in this secondary, but important, binary outcome. Estimates of power to detect differences in the proportion of probable cases of MDD as indicated by the PHQ-9 at 6-month follow-up were based on the estimated rate of onset of MDD in our target group and the anticipated effect of the SHUTi intervention. Based upon data from a subsample of participants in the PATH Through Life study [61] with comparable initial depression scores, and adjusting for the length of observation (6 months for this study vs. 4 years for PATH), approximately 15% of the no-intervention group with subclinical levels of depressive symptoms is expected to progress to probable MDD (a score of 15 or above on the PHQ-9, classified as moderately severe to severe depression and indicative of probably MDD [62]) within 6 months. We expect, based on data from previous research utilising SHUTi, a reduction of 40% of incident episodes in the treated group. For a total sample of 80% power, with a 40% reduction in risk in a sample with a pre-test incidence rate of 15%, a total sample size of 972 is needed. Economies of scale inherent in our automatised trial implementation should allow us to recruit a total sample of 1,600. This will maintain power if the incidence rate proves to be only 10% (total sample needed = 1,526) or if recruitment rates are less than anticipated. The target sample size will also maintain a power of 80% if the efficacy of the intervention is as low as 30%.

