### Assessments

Assessments are completed at pretest; immediate post-test; and 6-, 12-, and 18-month follow-up. Pretest assessment includes demographic information; outcome measures pertaining to insomnia (Insomnia Severity Index-ISI [46]), depression symptomatology (PHQ-9 [41]), anxiety (Generalised Anxiety Disorder, 7 items-GAD-7 [47]), suicidal ideation (from the Psychiatric Symptom Frequency scale-PSF [48]), disability (World Health Organisation Disability Assessment Schedule, 12 items-WHODAS-12 [49]), physical health and physical activity (International Physical Activity Questionnaire, Short Form-IPAQ SF [50]), attitudes toward help-seeking (Actual Help Seeking Questionnaire-AHSQ [51]/General Help Seeking Questionnaire-GHSQ [52]), and potential correlates of treatment outcome such as dysfunctional beliefs about sleep (Dysfunctional Beliefs About Sleep measure-DBAS [53]), sleep-threat monitoring (Sleep-Associated Monitoring Index-SAMI [54]), condition preference, and perceived need for treatment. Participants’ cognitive functioning will also be measured during the telephone-based diagnostic interview (Brief Test of Adult Cognition via Telephone-BTACT, Speed of Processing Subscale [55]). During the intervention phase of the study, participants will complete ongoing assessments on the ISI [46,56] and, to measure ongoing depression and anxiety symptomatology, the PHQ-9 [41] and GAD-7 [47] respectively at weeks 2, 4, 6, and 8.

At post-test, participants will complete an online questionnaire similar to that at pretest (see Table 1) in addition to receiving a telephone call in which they will again be administered the MINI [42] and the BTACT [57].

**Table 1 T1:** Assessment measures in the GoodNight study

	**Online screener**	**Screening telephone interview**	**Pre-****test survey**	**During intervention**	**Immediate post-****test**	**6-, ****18-****month f/****u**	**12-****month f/****u**
**PHQ**-**9**^ **1** ^	X		X	X	X	X	X
**BIS**^ **2** ^	X						
**Secondary eligibility criteria**	X						
**MINI**^ **3** ^		X			X	X	
**Adapted Morin insomnia interview**		X					
**BTACT**^ **4** ^		X			X	X	
**Demographics**			X				
**Condition preference**			X				
**Perceived need for treatment**			X				
**GAD-****7**^ **5** ^			X	X	X	X	X
**PSF**^ **6 ** ^**(suicidal ideation items)**			X		X	X	X
**DBAS**-**16**^ **7** ^			X		X	X	X
**SAMI**^ **8 ** ^**(shortened)**			X		X	X	X
**IPAQ SF**^ **9** ^			X		X	X	X
**AHSQ/****GHSQ**^ **10** ^			X		X	X	X

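### The power section uses a 6-month onset rate as if it were the proportion at PHQ-9 15 or above at one visit, so 80% power at 972 is not supported for that comparison

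*Protocol article*

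**What the plan says.** All of this is in the Power section of the protocol article unless stated otherwise.

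- **Outcome and input, in one sentence:** "proportion of probable cases of MDD as indicated by the PHQ-9 at 6-month follow-up were based on the estimated rate of onset of MDD". A probable case is a score of 15 or above at that visit.
- **Source of the control figure:** a cohort subsample, after "adjusting for the length of observation (6 months for this study vs. 4 years for PATH".
- **Control figure:** "approximately 15% of the no-intervention group with subclinical levels of depressive symptoms is expected to progress to probable MDD". The cut-off is described as "classified as moderately severe to severe depression and indicative of probably MDD [62]) within 6 months".
- **Effect:** "a reduction of 40% of incident episodes in the treated group".
- **Totals:** 972 for 80% power at 15%; 1,526 if the rate is 10%; 1,600 to be recruited.

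The inclusion criteria admit PHQ-9 scores above 4 and below 20, and exclude current MDD by the MINI rather than by a PHQ-9 cut-off. The hypotheses section lists, as a secondary outcome, MINI depressive episodes occurring since pre-test, assessed at 6 months. The Assessments section schedules "the PHQ-9 [41] and GAD-7 [47] respectively at weeks 2, 4, 6, and 8", and Table 1 adds pre-test, post-test and the follow-ups.

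**The concern.** A proportion at a visit and an onset rate over a period are different quantities. A rate scaled by length of observation counts people who cross the threshold at some time in the window. The visit counts people who are above it on the day. The two are equal only if nobody who crosses returns below 15 before the visit and nobody is at 15 or above at entry. The protocol claims neither, and its own entry criteria make the second doubtful.

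Remission lowers the visit proportion. Entrants already at 15 to 19 raise it, but they are not incident episodes, and the 40% is stated only for incident episodes. Both the event count and the size of the difference behind the 80% are therefore open. So is the margin between 972 and 1,600, which the section offers as cover for a lower rate, weaker recruitment or a smaller effect.

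**Working it through.** **Inputs from the Power section:** control rate 15%, relative reduction 40% (so 9%), totals 972, 1,526 and 1,600.

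**Assumptions:** 1:1 allocation, two-sided 5% Fisher exact test, everyone observed, onsets uniform over the window, exponential time above the cut-off with mean *D* months. The documents give no value of *D* and no share of entrants at 15 or above, so both are shown over a range.

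**1. The plan's own figures.** Fisher power is 80.0% for 15% vs 9% at 486 per arm (972), and 80.0% for 10% vs 6% at 763 per arm (1,526). The normal approximation needs 920 and 1,442 without continuity correction, and 986 and 1,542 with it. The arithmetic is sound. It also shows that 15% and 10% went in directly as visit proportions, with no allowance for remission.

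**2. Remission, all entrants below 15.** The share of onsets still above the cut-off at 6 months is f = (D/6)(1 − e^(−6/D)). The control proportion is 0.15f and the treated proportion 0.09f.

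| D (months) | f | Control vs treated | Power at 972 | Power at 1,600 | Total for 80% |
|---|---|---|---|---|---|
| 3 | 0.432 | 6.5% vs 3.9% | 39.3% | 61.0% | about 2,450 |
| 6 | 0.632 | 9.5% vs 5.7% | 56.5% | 79.7% | about 1,650 |
| 12 | 0.787 | 11.8% vs 7.1% | 67.9% | 88.7% | about 1,300 |

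The uncorrected normal approximation is somewhat higher: 45%, 61% and 71% at 972.

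**3. Adding entrants already at 15 or above.** Let a share *s* start there, with r = e^(−6/D) of them still there at 6 months. Then:

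- control = s·r + (1 − s)·0.15·f
- treated, 40% on incident episodes only = s·r + 0.6·(1 − s)·0.15·f
- treated, 40% on all cases = 0.6 × control

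Example with s = 10% and D = 6: control = 0.10 × 0.368 + 0.90 × 0.15 × 0.632 = 0.0368 + 0.0853 = 12.2%. Treated is 0.0368 + 0.6 × 0.0853 = 8.8% on the first reading and 0.6 × 12.2% = 7.3% on the second.

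| s | D (months) | Control | Incident only: power at 972 / 1,600 | All cases: power at 972 / 1,600 |
|---|---|---|---|---|
| 10% | 3 | 7.2% | 28.7% / 46.3% | 43.5% / 66.3% |
| 10% | 6 | 12.2% | 37.2% / 57.7% | 69.7% / 89.8% |
| 10% | 12 | 16.7% | 43.4% / 65.0% | 84.8% / 97.3% |
| 20% | 3 | 7.9% | 21.0% / 34.0% | 47.7% / 71.0% |
| 20% | 6 | 14.9% | 25.4% / 40.2% | 79.8% / 95.3% |
| 20% | 12 | 21.6% | 28.9% / 45.2% | 93.9% / 99.5% |

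**4. A longer onset window.** The abstract and Discussion count follow-up from the end of a 9-week programme, so the visit may fall about 8 months after pre-test. With the same onset rate per month and s = 0, control = 0.15 × (D/6)(1 − e^(−8/D)).

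- For D = 3, 6 and 12 this is 7.0%, 11.0% and 14.6%. Power at 972 is 42.3%, 64.5% and 78.7%; at 1,600 it is 64.8%, 86.2% and 94.8%.
- For D = 24 it is 0.15 × 4 × (1 − e^(−1/3)) = 17.0%, above 15%, so power at 972 exceeds 80%.

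**The case against.** The strongest reply is that the direction is not fixed. A reader might infer that 80% at 972 is simply overstated, but that needs the visit proportion, or the difference between arms, to be smaller than assumed. The documents give no persistence figure and no baseline distribution of PHQ-9. Entrants at 15 to 19 and an 8-month window can each bring the visit proportion back to 15% or more. This stands, and the conclusion has to be conditional. It is only a partial rescue, however: restoring power through baseline cases requires the 40% to apply to them too, and the section states it only for incident episodes. Otherwise they dilute the difference.

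It may also be said that the 15% might derive from case status at a later wave of the source cohort. That source is not at hand. On the protocol's own wording, though, the figure is an onset rate adjusted for length of observation, and a visit proportion would not ordinarily be scaled that way.

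Finally, the consequences are limited. The plan recruits 1,600, tests a 10% rate itself, and has the continuous PHQ-9 score as its primary outcome. The MINI secondary outcome is already a period measure. These points stand. They reduce the weight of the concern but do not make the rate and the powered outcome the same quantity.

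**Conclusion.** The Power section equates onset over 6 months with status at one 6-month visit, and so leaves out both remission and entrants already at 15 or above. The stated 80% at 972 is not supported for the single-visit PHQ-9 comparison.

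- It is overstated if some onsets remit and all entrants start below 15, with onsets spread over 6 months: about 39% to 68% at 972 and 61% to 89% at 1,600 for mean spells of 3 to 12 months.
- It is overstated if baseline cases count and the 40% applies only to incident episodes: about 21% to 43% at 972 and 34% to 65% at 1,600, for 10% or 20% of entrants at 15 or above.
- It may reach 80% or more if the 40% extends to existing cases, or if spells are long and the onset window is about 8 months.

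Spell lengths and baseline shares are assumptions, and all figures take everyone as observed. Two stronger readings are not supported. The sample-size arithmetic is not wrong, since both totals reproduce. Nor do the documents show that 1,600 is too few: several scenarios keep 80% or more there, and this says nothing against power for the continuous primary outcome.

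**What to change.** Make the rate and the outcome the same quantity, in one of two ways.

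**Keep the single-visit comparison.** Replace 15% by the proportion expected at 15 or above at the 6-month visit. State how entrants at 15 to 19 are counted and whether the 40% applies to them. Then restate the total for 80% power, and the power at 1,600, over a stated range of persistence.

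**Keep 15% as an onset rate and power a period outcome.** This can be the MINI incidence since pre-test, already a secondary outcome, with a statement of why a rate defined by PHQ-9 15 or above carries over to the MINI. Or it can be a first PHQ-9 of 15 or more at any scheduled assessment up to 6 months, among those below 15 at pre-test. The restriction matters: without it, an entrant who stays at 15 to 19 would be scored as an onset.

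The cost is a reworded paragraph, a short table and, for the PHQ-9 version, one variable derived from assessments already scheduled. The downsides are that the stated power may become less favourable, and that the PHQ-9 period outcome drops baseline cases, misses short spells between post-test and 6 months, and needs a rule for missed interim surveys.

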### Statistical analysis

Primary analyses will be undertaken on an intent-to-treat (ITT) basis, including data for all participants who were randomised, irrespective of their level of adherence to the intervention or whether they withdrew at any point in time. Participants with missing data will be accommodated using linear and generalised mixed-model repeated measure (MMRM) models. Transformations, including dichotomisation or other categorisation, will be undertaken as necessary to meet distributional assumptions and to accommodate outlying observations.

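### The claim that recruiting 1,600 keeps 80% power at 10% incidence compares participants recruited with participants observed: 1,526 has no allowance for loss to follow-up.

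*Protocol article*

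**What the plan says.** The Power section bases the sample size on a binary secondary outcome, probable MDD on the PHQ-9 at 6-month follow-up. The primary outcome is the continuous PHQ-9 score.

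- Base case: "approximately 15% of the no-intervention group with subclinical levels of depressive symptoms is expected to progress to probable MDD", with "a reduction of 40% of incident episodes in the treated group", and for 80% power "a total sample size of 972 is needed".
- Target: the automated design "should allow us to recruit a total sample of 1,600".
- Fallback for a lower event rate: "This will maintain power if the incidence rate proves to be only 10% (total sample needed = 1,526".
- A second fallback is joined to it by the word or: "or if recruitment rates are less than anticipated".

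The Power section has no term for loss to follow-up. The Statistical analysis section applies intention to treat to everyone randomised, including those who withdraw, and adds: "Participants with missing data will be accommodated using linear and generalised mixed-model repeated measure (MMRM) models".

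**The concern.** The fallback sentence sets a required number (1,526) beside a recruited number (1,600) and concludes without condition that power is kept. That follows only if 1,526 already allows for loss or if almost everyone recruited supplies a 6-month outcome. The outcome is measured six months after a 9-week online self-help programme, and the plan itself provides for withdrawal and missing data.

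The stake is how a null caseness result would be read. If incidence turned out near 10%, which is the situation the sentence was written for, such a result would be judged against a claimed 80% power that the trial might not have had.

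**Working it through.** **Inputs from the Power section.** Power 80%; control rate 15% (base) or 10% (fallback); relative reduction 40%, so 15% against 9% and 10% against 6%; stated totals 972 and 1,526; target 1,600.

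**Assumptions.** 1:1 allocation and two-sided alpha 0.05; the article states neither. All loss rates below are also assumptions, since the article gives none.

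**1. Reproducing the stated totals**

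Uncorrected chi-square, per arm:

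n = [1.96·√(2p̄(1−p̄)) + 0.8416·√(p₁(1−p₁) + p₂(1−p₂))]² / (p₁−p₂)²

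For 10% against 6%, p̄ = 0.08. This gives n = 721 per arm, or 1,442 in total. The same formula for 15% against 9% gives 920. Neither matches the stated figure.

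With the continuity correction the totals are 1,542 and 986, within 1.0% and 1.4% of the stated 1,526 and 972.

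Exact power of the two-sided Fisher test is 80.0% at 486 per arm (972) for 15% against 9%, and 80.0% at 763 per arm (1,526) for 10% against 6%. Both stated totals are therefore recovered by a Fisher-type calculation, and no attrition term is needed. They are numbers of observed outcomes.

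**2. The margin**

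- 10% incidence, Fisher: 1,600 − 1,526 = 74, and 1 − 1,526/1,600 = 4.6%.
- 10% incidence, uncorrected chi-square: 1 − 1,442/1,600 = 9.9%.
- 15% base case, Fisher: 1 − 972/1,600 = 39%.

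**3. Power for 10% against 6% when only observed outcomes count**

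| Assumed loss from 1,600 | Observed | Fisher | Uncorrected chi-square |
|---|---|---|---|
| 0% | 1,600 | 82% | 84% |
| 4.6% | 1,526 | 80% | 82% |
| 10% | 1,440 | 78% | 80% |
| 20% | 1,280 | 72% | 75% |
| 30% | 1,120 | 66% | 69% |
| 40% | 960 | 59% | 63% |

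For comparison, the base case of 15% against 9% still has 86% power (Fisher) at 30% loss.

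**4. Low recruitment together with low incidence**

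The surplus over the base case is 1,600 − 972 = 628. Moving to 10% incidence uses 1,526 − 972 = 554 of it and leaves 74. If 1,550 were recruited, the tolerable loss at 10% incidence would be 1 − 1,526/1,550 = 1.5%. At 1,526 recruited it would be zero.

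**The case against.** **The arithmetic is right and the article is condensed.** Both totals reproduce, and 1,600 does exceed 1,526. An expected loss rate may stand in the full protocol or the analysis plan, so its absence here is not in itself a fault. This stands. The point rests on a sentence that the article does contain, which states without condition that power is kept.

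**The 4.6% limit depends on the test.** This also stands. It belongs to the conservative calculation that reproduces 1,526. With an uncorrected chi-square about 10% loss is tolerable, and at 10% loss the shortfall is only 0 to 2 percentage points. Larger deficits need losses of 20% or more.

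**Mixed models use partial data.** The PHQ-9 is also collected at pretest, at weeks 2, 4, 6 and 8, and at post-test. A missing 6-month value therefore need not cost information one for one, and the table in the working leans to the pessimistic side. But a model does not recreate unobserved 6-month outcomes, and the stated totals come from a simple two-proportion calculation that claims no gain from repeated measures.

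**Stronger readings that the article does not support.** A reader might infer that it promises cover for low incidence and low recruitment together. It joins them with or, each against the base case, and at 15% incidence recruitment could fall well short of 1,600 without harm. A reader might also infer that the trial as a whole is underpowered. The base case has ample room, and nothing here touches the continuous primary outcome. Nor do the documents establish any particular loss rate.

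**Conclusion.** The point holds in a limited form. The totals of 972 and 1,526 are participants with an observed 6-month outcome, so the unconditional statement that 1,600 recruited keeps 80% power at 10% incidence is not supported. It is true only with loss of at most 4.6% (Fisher-type) or about 10% (uncorrected chi-square). Beyond that, power falls to roughly 72–75% at 20% loss and 66–69% at 30%, less whatever a mixed model recovers. This rests on 1:1 allocation, a two-sided 5% test and assumed loss rates.

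The scope is one fallback scenario for a secondary outcome. It is worth correcting because caseness was chosen as the basis for the sample size.

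The next sentence of the Power section, on 30% efficacy, should not be read as another instance of this problem. At a 15% control rate (15% against 10.5%) it fails with no loss at all: power at 1,600 is 75.0% (Fisher) or 77.0% (chi-square). It needs its own correction.

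**What to change.** In the Power section:

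1. Label 972 and 1,526 as participants with an observed 6-month outcome, and name the test, alpha and allocation ratio behind them.
2. Replace the unconditional statement for 10% incidence with power over a range of losses, for example 10 to 40%, and mark the losses as assumptions unless an expected rate can be cited. Say that the 15%/40% case tolerates about 39% loss.
3. Add that low incidence and low recruitment cannot both be covered, since only 74 participants remain once incidence is 10%.
4. If credit is to be taken for earlier PHQ-9 scores in the mixed model, support it with a calculation for that model.

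The cost is a rewording of one paragraph with figures already computed; step 4, if taken, needs one further calculation. No extra participants and no change of design are required.

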Cognitive Behavioural Therapy for Insomnia (CBT-I) is amongst the most effective treatments for insomnia [26]; it is as effective as pharmacotherapy in the long term, with the added benefit of improvements persisting beyond cessation of treatment [27] and without the possible side effects. Recent evidence also suggests that CBT-I can have the benefit of reducing comorbid depression, decreasing both depression-related sleep-disturbance [28,29] and depressive symptomatology [19,29]. There is preliminary evidence suggesting that Internet-based CBT-I in individuals reporting with insomnia also results in reduced levels of depressive symptoms, in addition to significantly reducing insomnia [30]. However, the question of whether major depressive episodes can be *prevented* by treating insomnia has not yet been answered.

The current trial uses a cognitive behaviour therapy (CBT) intervention for sleep, delivered as a web-based programme, SHUTi [31]. The choice of an online application such as SHUTi was motivated by the observation that Internet programmes can offer the intervention to a large number of individuals [32]. Online interventions, if effective, have wide-scale reach and can be disseminated for little cost [33], making them ideal for prevention at a population level. They are also often preferred over traditional face-to-face methods for their ability to provide anonymity, convenience, and ability to be used at home [34].

Sixteen hundred community-dwelling adults from Australia will be randomised to one of two conditions: SHUTi, an online Cognitive Behavioural Therapy intervention for Insomnia, shown to be effective in decreasing insomnia severity and improving sleep efficiency in two US trials [31,35], or HealthWatch, an attention-matched control condition used in previous RCTs run through the Centre for Mental Health Research, ANU [36,37].

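### With 1,600 participants, power for a 30% reduction in probable MDD is about 75%, not the 80% the protocol states

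*Protocol article*

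**What the plan says.** The Power section of the protocol article explains that the sample size rests on a binary secondary outcome rather than on the continuous primary one. It describes "Estimates of power to detect differences in the proportion of probable cases of MDD as indicated by the PHQ-9 at 6-month follow-up", with a case defined as a PHQ-9 score of 15 or above.

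- **Control rate:** "approximately 15% of the no-intervention group with subclinical levels of depressive symptoms is expected to progress to probable MDD" within 6 months.
- **Planned effect:** "a reduction of 40% of incident episodes in the treated group".
- **Base case:** "with a 40% reduction in risk in a sample with a pre-test incidence rate of 15%, a total sample size of 972 is needed" for 80% power.
- **Target:** economies of scale "should allow us to recruit a total sample of 1,600".
- **First reserve case:** "This will maintain power if the incidence rate proves to be only 10% (total sample needed = 1,526").
- **Second reserve case:** "The target sample size will also maintain a power of 80% if the efficacy of the intervention is as low as 30" per cent.

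A required total is printed for the base case and the first reserve case. None is printed for the second. The section does not name the test, the significance level, its sidedness or any dropout allowance.

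**The concern.** The required sample size rises roughly with the inverse square of the difference between the two rates. Going from a 40% to a 30% reduction at a 15% control rate shrinks the difference from 6 to 4.5 percentage points. Multiplying 972 by (6/4.5)² = 1.78 gives about 1,728 before any change in variance, which already exceeds 1,600.

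The sentence is the protocol's assurance about an effect smaller than planned, on the outcome that set the sample size. If it is wrong, anyone judging how informative a non-significant caseness result is would credit the trial with more sensitivity than it has. The section also offers the same 1,600 as cover for lower recruitment. In the 30% case there is nothing to spare even at full recruitment.

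**Working it through.** **Inputs from the Power section.** Control rate 15% (10% in the first reserve case); relative reduction 40% or 30%; power 80%; total 1,600.

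**Assumptions, because the article does not state them.** Two-sided 5% test, 1:1 allocation, everyone analysed. Step 1 supports them.

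**Step 1. Reproduce the printed totals.** The test is Fisher's exact test with 2.5% in each tail. Its power is found by summing the binomial probabilities of all outcomes that reach significance.

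| Contrast | Total N | Power |
|---|---|---|
| 15% vs 9% | 970 | 0.7991 |
| 15% vs 9% | **972** | 0.8000 |
| 10% vs 6% | 1,524 | 0.7999 |
| 10% vs 6% | **1,526** | 0.8004 |

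Both printed totals are matched exactly, with no dropout inflation. Other two-sided formulas come less close:

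- Pooled normal, no continuity correction: 920 and 1,442.
- Pooled normal, continuity-corrected: 986 and 1,542.
- Arcsine, continuity-corrected: about 973 and 1,521.
- One-sided 5% testing gives only 724 to 790 and 1,136 to 1,234, so it cannot be the source.

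**Step 2. Apply the same test to the 30% case.** The treated rate is 0.15 × (1 − 0.30) = 0.105.

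| Contrast | Total N | Power |
|---|---|---|
| 15% vs 10.5% | 1,600 | **0.7502** |
| 15% vs 10.5% | 1,796 | 0.7999 |
| 15% vs 10.5% | 1,798 | 0.8004 |

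**Step 3. Repeat with a more lenient formula.** For the uncorrected pooled normal test, the number per arm is

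n = [z₀.₉₇₅ √(2p̄(1−p̄)) + z₀.₈₀ √(p₁(1−p₁) + p₂(1−p₂))]² / (p₁−p₂)²

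with p̄ = (0.15 + 0.105)/2 = 0.1275.

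- First term: 1.960 × √0.22249 = 0.9245.
- Second term: 0.8416 × √(0.1275 + 0.0940) = 0.3961.
- n = (0.9245 + 0.3961)² / 0.045² = 1.7439 / 0.002025 = 861.2 per arm, so 1,722 in total, or 1,724 with each arm rounded up.
- Power at 800 per arm: Φ[(0.045 × √800 − 0.9245) / 0.4706] = Φ(0.740) = 0.770.

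The unpooled formula needs about 1,718 and the arcsine formula about 1,714, or 1,717 and 1,712 before rounding each arm up. They give 77.2% and 77.3% power at 1,600. The continuity-corrected formula needs about 1,812 and gives 74.7%.

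**Step 4. Find what 1,600 does detect from a 15% control rate.**

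| Reduction | Fisher | Pooled normal |
|---|---|---|
| 30% | 75.0% | 77.0% |
| 31% | 78.0% | 79.9% |
| 32% | 80.8% | 82.5% |

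The smallest reduction with 80% power is about 32% by Fisher and about 31% by the uncorrected formula.

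**Step 5. Illustrate loss to follow-up.** The loss rates are assumptions; the article gives none. For 15% versus 10.5%, with only completers analysed:

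- 20% lost (1,280 analysed): 64.7% by Fisher, 67.5% by pooled normal.
- 30% lost (1,120 analysed): 58.7% by Fisher, 61.7% by pooled normal.

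**The case against.** The strongest reply is that the error is small and changes no decision. The planned effect is a 40% reduction, and the two totals that support 1,600 are correct. The outcome is secondary. The control rate is itself only approximate: by the uncorrected formula, a rate of 16% would bring power for a 30% reduction to 80.0%. All of this is true, and it limits the consequence. It does not make the sentence correct, because 15% is the rate the section states. By the test that reproduces the printed totals, 16% gives 78.2% and 16.5% gives 79.7%, so a rate nearer 17% would be needed.

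A second reply is that the article names no test, so Fisher is an inference. That is fair, and arcsine with continuity correction comes close to both totals. The conclusion does not depend on the choice: every two-sided 5% method tried gives less than 80% at 1,600. One-sided testing at 5% would give about 84 to 85%, but it cannot produce 972 or 1,526.

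A third reply is that the planned mixed models use partial data, so completer power is not the power of the planned analysis. This stands, and the loss figures in Step 5 are illustrations only. The printed claim comes from a comparison of two proportions and fails there with complete data.

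**Conclusion.** The concern holds. At the stated 15% control rate, 1,600 participants give 75.0% power for a 30% reduction by the test that reproduces the protocol's other totals, and about 77% by the uncorrected formulas. Reaching 80% needs about 1,796, or at least about 1,712 under the most lenient of these formulas. The shortfall is about 5 points by the first method and 3 by the second.

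This rests on a two-sided 5% level, equal allocation and complete data. The first two are not stated in the article but are supported by the exact match to 972 and 1,526. The error is confined to one sentence about a secondary outcome.

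**What to change.** Replace the last sentence of the Power section with: *With 1,600 participants analysed (two-sided Fisher exact test, 5% level, equal arms), power to detect a 30% reduction from a control rate of 15% is about 75%; the smallest reduction detectable with 80% power is about 32%.*

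The authors should confirm the test. If they used an uncorrected chi-square for this sentence, the figures become about 77% and 31%, but that formula does not give 972 or 1,526. Naming the test and level here simply makes the restated figures checkable.

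The cost is one reworded sentence and a slightly less favourable figure. The sample size, conduct and primary analysis stay as they are.
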